### Recruitment

#### Identification of care homes and approach

Care homes will be identified from Care Quality Commission lists with the advice of the local Tissue Viability Service. The homes will be sent a study brochure to invite them to express an interest in taking part. Staff from interested homes will be invited to a study event at which the study protocol will be explained in a group setting. All homes expressing interest will be visited by a research nurse to explain the study in more detail and confirm willingness to take part. All care homes that take part will be required to sign a letter of agreement to acknowledge their understanding of what their involvement entails. At this set-up visit, the research nurse will provide study-specific training for the staff and will also identify potentially eligible residents.

The research nurses will not provide any clinical management; their role is primarily to establish contact with potential participants and manage the collection of study data. If, however, during the conduct of the study, the research nurse notices any condition not related to the study which, in their professional opinion requires attention, they have a duty of care to report this to the care home manager.

#### Recruitment of care home residents

Potentially eligible residents will be identified to the research nurse by care home staff at the home’s set-up visit (Visit 1). The research nurse will approach potential participants, explain the study, show the resident a sample of the protective socks and leave written information (i.e. the Research Ethics Committee (REC) approved Participant Information Sheet). Care home staff will be provided with a site file containing essential documents and contact details (mobile telephone numbers and email addresses) for the research nurse.

#### Informed consent

The research nurse will return within a day or two (ensuring residents have had sufficient time to read, understand and discuss the Participant Information Sheet) to answer questions and ask whether the potential participants would like to take part in the study. The research nurse will be responsible for adjudging the residents’ capacity to provide informed consent, and this will be achieved through discussion with the resident to determine whether or not the study information has been retained and understood. The research nurse will consider the guidance in the Mental Capacity Act 2005 Code of Practice when assessing mental capacity. Those who do wish to take part will be asked to give their formal consent by signing the consent form. The written informed consent process will be undertaken by the research nurse who will be trained in Good Clinical Practice and the informed consent process.

#### Recruitment of patients from the community

Study entry criteria remain the same for this group of participants except that they do not need to be resident in a care home. Time points for data collection and the outcome data items collected will be the same.

#### Participant identification via Primary Care

The Clinical Research Network (South West Peninsula) will support the identification and recruitment of research active general practices (GPs) into the study. Practices that decide to participate will be contacted by the research nurse to discuss the requirements of the study and the search criteria. GP staff will search for patients aged 65 years or older who have used oral steroids for more than a month in the prior 12 month period. Lists generated from the search will be screened for suitability by a doctor at each participating practice and unsuitable patients excluded, e.g. those with terminal illness, mental illness etc. A member of the practice staff will send suitable patients an invitation letter on GP headed paper, including a study reply form and reply-paid envelope. Patients are asked to return the reply form to the research team if interested in receiving more information about the study. Patients that respond to say that they are interested in receiving more information will be contacted by a member of the research team and an appointment made for the research nurses to meet with the patient. The GP may send one follow-up letter to all the patients originally invited with a sentence advising that the letter should be ignored if they have already responded. Patients who return the reply form to the research team will then undergo the recruitment process described below.

#### Participant identification via the NIHR Exeter Clinical Research Facility

Potential participants may also be identified via the “Exeter 10000” research volunteer bank managed by the NIHR Exeter Clinical Research Facility (Exeter CRF). The volunteer bank database will be searched by authorised members of the Facility for volunteers aged 65 years and older who have used oral steroids for more than a month in the prior 12-month period. A member of the facility staff will send suitable volunteers an invitation letter on Exeter CRF headed paper, including a study reply form and reply-paid envelope. Volunteers will be asked to return the letter (including the reply form) to the Exeter 10000 team who will forward their name to the research team if interested in receiving more information about the study. Volunteers who return the reply form will then undergo the recruitment process described below.

#### Community recruitment process

On receipt of a completed reply form, a research nurse will telephone the patient or volunteer using the contact details provided on the reply form, once the person has had at least 24 h to read the study information. The research nurse will ascertain potential eligibility by explaining the full study entry criteria to the person. If the research nurse is satisfied that the person is potentially eligible, and willing to take part, the research nurse will arrange a visit at which eligibility will be confirmed and informed consent obtained. Visits may be performed at persons’ homes or at a local community hospital or GP surgery if mutually convenient.

#### Informed consent, randomisation and baseline assessment of community participants

At this initial visit, the research nurse will explain the study and demonstrate a pair of the protective socks. The written informed consent process will be undertaken by a research nurse trained in GCP and the informed consent process. Having reconfirmed eligibility, those who do wish to take part will be asked to give their formal consent by signing the consent form. Baseline measures and randomisation will then be performed as per protocol. On successful completion of this visit, the REC approved GP letter will be posted to the participant’s GP, if the participant consents to their GP being informed.

#### Participant retention

Plans to promote participant retention and complete the follow-up include encouragement from the research nurses who will be in regular telephone and face-to-face contact with the participants, whether resident in a care home or living independently in the community.

### Intervention group

The protective socks are manufactured by Dermatuff Limited. The socks are CE marked and are registered with the Medicines and Healthcare products Regulatory Authority (MHRA) as “Skin Tears Protection System Wear”, a Class I Medical Device. Materials used in the manufacture of the socks are in conformity with all relevant and required standards including the ISO 10993 series evaluating biocompatibility of a medical device prior to a clinical study.

The research nurse will carry a stock of protective socks and, before leaving the care home, the research nurse will visit those randomised to wear protective socks to provide socks of the correct size. The socks are available in a choice of grey or beige colour. The choice of colour will be recorded by the research nurse. Three pairs of socks will be provided to the care home for each participant in the intervention group. The participants will be able to keep these socks at the end of their participation in the study.

The participants in the intervention group will be asked to wear the protective socks during their waking hours every day for a period of 16 weeks, starting from the morning following the day they sign consent, which will be designated as “Day 1.” Care home staff will be asked to encourage participants to wear the socks and to assist them to put the socks on, if necessary. However, it will be emphasised that if participants become unwilling to wear the socks or want to take them off, they will be free to make that choice. The participants should continue to wear their normal footwear during participation in the study.

#### Participant diary

The participants in the intervention group will be given the first of 16 weekly diaries at this visit and will be asked by the research nurse to complete the diary on a daily basis. The participants will be asked to use the diary to record the extent to which they wear the socks each day and the reasons for removing them (if applicable), plus any negative or positive comments about wearing the socks. A new weekly diary will be provided to the participant each week.

### Control group

The participants in the control group will be managed as usual. This includes any routine procedures to reduce the risk of lacerations, but otherwise they will wear their normal clothing. At the end of their participation, each participant from the control group will be offered one pair of socks to keep for their own use.

### Outcome measures

The measures proposed for a future definitive trial will be collected in this pilot study. The primary outcome of a future trial will focus on skin-tear free days and the incidence and severity of skin tears.

#### Procedure in the event of a skin tear injury

Care home staff or the community participant themselves will be asked to contact the research nurse by telephone immediately on becoming aware of an injury (i.e. as soon as possible on the day of the injury or the following morning in the case of an overnight injury). The research nurse will visit the resident or patient as soon as practicable (within 1 to 2 working days) of being contacted in order to collect the following:Date and approximate time of injury.Brief description of injury cause.Type of lower leg clothing and footwear worn at the time of injury (including whether protective socks were in place for participants in the intervention group).Size of injury (length, width and total area using a grid tracing method).Category of injury using the Payne-Martin and STAR classifications (as described in Appendix).A photograph of the injury.Information relating to the initial management of the injury (dressing type, referral to external healthcare professional such as GP, district nurse and hospital emergency department).

The research nurse will inspect the wound for signs of infection and will also check that the injury has been noted in the care home records (in the case of care home participants). Injured participants will complete outcome measure questionnaires 7 days post-injury.

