**Figure 1 Fig1:**
[figure not shown]
Participant pathway diagram (taken from the Participant Information Sheet).

**Table 1 Tab1:** Tabulated study schedule

Study procedure	Set up (Visit 1)	Baseline/Study Day 0 (Visit 2)	Study Day 1 (the day after consent)	Upon new injury	Weekly* for 16 weeks	Study Day 112	Qualitative data collection
Identify potentially eligible participants	X						
Provide Participant Information Sheet	X						
Informed consent		X					
Collection of baseline information		X					
EQ5D-5 L questionnaire		X		X^c^		X	
ICECAP-O questionnaire		X		X^c^		X	
FES-I (short) questionnaire		X		X^c^		X	
Randomisation		X					
Provision of socks (intervention arm only)		X					
Wearing of socks (intervention arm only)			X --------------------------------- > X				
Completion of participant diary (intervention arm only)			X --------------------------------- > X				
Photograph wound				X^b^			
Measurement of wound				X^b^			
Wound scoring				X^b^			
Cardiff wound impact schedule^a^				X^c^		X^d^	
Adverse event recording			X --------------------------------- > X^e^				
Research nurse to visit care home for progress checks					X		
Patient interviews							X
Focus groups							X

^*^Regular contact (visit or telephone), approximately weekly.

^a^Completed only by participants who experienced one or more skin tear injuries during their study participation.

^b^Performed within one working day following injury.

^c^Performed seven days post-injury.

^d^Completed on Day 112 by all participants who experienced skin tear injury during the study. In addition, participants who incur an injury during week 16 (Day 106 to 112 inclusive), will also complete the questionnaire seven days post-injury.

^e^Day 112 or Day 112 + 1 to 7 days if a skin tear injury occurs during week 16.

**Table 2 Tab2:** Main eligibility criteria (inclusion and exclusion criteria)

Inclusion criteria	Exclusion criteria
Resident in a care home or living in the community and at high risk of skin tears.	Not competent to give informed consent in the opinion of the recruiting nurse.
Aged 65 years or older.	Bedbound.
Ambulatory and/or wheelchair user able to take part in daily activities within a care home or in the community.	Being treated for current lacerations or ulcers on their legs.
	Participant likely to use graduated compression stockings or similar during the intervention period.

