### Trial objectives

This pilot study is intended to pave the way for a definitive randomised controlled trial assessing the effectiveness and cost-effectiveness of the new socks in protecting the lower legs. The aim of this pilot study is to provide the necessary information for the planning of the future trial. It will test the feasibility of running such a trial and provide estimates of recruitment (care homes and residents, and patients in primary care), trial attrition, completion of questionnaire-based quality of life measures, baseline scores and standard deviations of those measures in this population. It will test the feasibility of gathering data on skin tears occurring in care homes and in the community by research nurses. It will assess the acceptability of using the protective socks and also of participating in the trial. It will provide useful information about the distribution of the variables to inform the sample size calculation for a larger trial. It will also provide an estimate of the impact of any contamination (during subsequent interviews).

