### Secondary outcomes

#### Skin tear assessments

There is no universally accepted classification system for the assessment of skin tears. Payne and Martin developed the first classification system in 1990, and this was updated in 1993 [1]. Problems associated with inter-rater reliability testing of the Payne and Martin classification system, and its poor utility in Australia, led to a study that resulted in the Skin Tear Audit Research (STAR) Classification System. The STAR Classification System is commonly used in Australia, with evidence of implementation reported within the UK [30].

In the main trial, skin lacerations will be measured in centimetres (length, breadth and area) and graded either according to Payne-Martin categories or the STAR Skin Tear Classification System. The photographs will inform an assessment of the reliability of the reported grading of the injury and will be performed by a tissue viability nurse specialist blinded to allocation.

Skin tear assessments will be performed upon learning of an injury, within 24 h if possible.

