#### Other secondary outcome measures

Standardised measure of health status (EQ-5D-5L): collected at baseline, 16 weeks and in the event of a skin tear injury.Assessment of capability (ICECAP-O): collected at baseline, 16 weeks and in the event of a skin tear injury.Assessment of fear of falling (Short FES-I): Collected at baseline, 16 weeks and in the event of a skin tear injury.Disease-specific quality of life measured by Cardiff Wound Impact Schedule: Collected in the event of a skin tear injury and at 16 weeks (from participants who have had a skin tear).Adverse events caused by the socks.Health care resource use: collected in the event of a skin tear injury.Outcome measures for the pilot study are:Recruitment rate for homes.Proportion of participants (home residents) eligible.Recruitment rate for participants.Attrition and loss to follow up.Ascertainment of injuries.Completion and completeness of study questionnaires.Estimates of the distribution of outcome measures.Feasibility of the workload.Acceptability of the intervention to participants.Acceptability of study participation to participants.

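### Ascertainment of injuries is a pilot outcome, but the one check described covers only tears already reported; the wound assessment windows also need reconciling

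*Protocol article*

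**What the plan says.** The list of pilot outcomes at the end of Other secondary outcome measures includes "Ascertainment of injuries". Trial objectives gives the aim behind it: "It will test the feasibility of gathering data on skin tears occurring in care homes and in the community by research nurses". The article attaches no numerator or denominator to this outcome.

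Under Procedure in the event of a skin tear injury, care home staff or the community participant "will be asked to contact the research nurse by telephone immediately on becoming aware of an injury". The nurse then visits, collects the injury data and "will also check that the injury has been noted in the care home records". The same sentence limits this check to care home participants.

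Three places give the timing of the wound assessment:

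- Table 1, note b, for photograph, measurement and scoring: "Performed within one working day following injury".
- Procedure in the event of a skin tear injury, for the visit that collects the same items: "as soon as practicable (within 1 to 2 working days) of being contacted".
- Skin tear assessments: "Skin tear assessments will be performed upon learning of an injury, within 24 h if possible".

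**The concern.** A pilot that names ascertainment as an outcome should be able to say what share of the tears that occurred reached the trial. The check described takes a reported tear and looks for it in the home's notes. The question needs the opposite direction: take the tears in the notes and ask which were reported. Community participants have no check of either kind.

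Missed reports are plausible on the article's own account. The Background says that older people may be less aware of an injury because pain perception and touch are reduced, yet in the community a report depends on the participant noticing. The Sample size section expects 40 per group to give sound estimates of incidence and skin tear-free days, and Statistical methods carries the outcomes forward to size the definitive trial. If reporting is incomplete, those inputs are affected, and the check described would not show it.

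The timing conflict is a smaller, separate matter. Two places set different limits, counted from different start points, for the same assessment.

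**Working it through.** No stated figure is in dispute, so there is none to reproduce. Two checks of logic apply.

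**1. What the record check can estimate**

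Classify the tears by whether they were reported to the nurse and whether they are in the home's records:

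- a = reported and recorded
- b = reported, not recorded
- c = recorded, not reported

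The check described gives a / (a + b), the completeness of the records among reported tears. Completeness of reporting among recorded tears is a / (a + c). The check never observes c.

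Illustration, all values assumed: N = 20 true tears, each recorded with probability r = 0.8, independently of being reported with probability s. Then a = N·s·r, b = N·s·(1 − r), c = N·(1 − s)·r.

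| True share reported, s | a | b | c | Check described, a/(a+b) | Reverse check, a/(a+c) | Share of known tears reported, (a+b)/(a+b+c) |
|---|---|---|---|---|---|---|
| 100% | 16.0 | 4.0 | 0 | 80% | 100% | 20/20 = 100% |
| 80% | 12.8 | 3.2 | 3.2 | 80% | 80% | 16/19.2 = 83% |
| 60% | 9.6 | 2.4 | 6.4 | 80% | 60% | 12/18.4 = 65% |
| 40% | 6.4 | 1.6 | 9.6 | 80% | 40% | 8/17.6 = 45% |

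The check described returns r in every row, so it carries no information on s. The last column is slightly optimistic because tears on neither list stay unknown, but it follows the true value down.

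**2. The assessment windows**

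Latest permitted day for the assessment, counted in calendar days from the injury:

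| Injury and report | Table 1 note b | Injury procedure (upper limit) | 24 h aim |
|---|---|---|---|
| Monday, reported the same day | +1 | +2 | +1 |
| Thursday, reported the same day | +1 | +4 | +1 |
| Thursday, reported the next day | +1 | +5 | +2 |
| Friday, reported the same day | +3 | +4 | +1 |

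A visit on the Wednesday after a Monday injury reported that day satisfies the injury procedure and breaches Table 1. Late reporting widens the gap, because Table 1 counts from the injury and the procedure counts from the contact.

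**The case against.** The strongest reply is that the telephone call is not the only route by which a tear can come to light. Table 1 schedules contact about weekly and care home progress checks. The Primary outcome section describes nurse visits at about the same interval and provides for a tear first found at week 16. The Background says tears can be slow to heal, so many would still be visible at the next visit. The interviews and focus groups also cover problems with data collection. This stands as far as it goes: a reader might infer that missed tears cannot be counted at all, and the article does not support that. But it does not say that these contacts include asking about or looking for new tears, or that such finds are tallied as missed reports. The stated purpose of wound inspection at the visits is to date healing. The full protocol may say more, but the article sets out the injury procedure item by item and fixes the direction of the check.

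Three other stronger readings are tempting:

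- **Reporting differs by arm.** Only sock wearers keep a diary ("The participants in the intervention group will be given the first of 16 weekly diaries at this visit"), and the trial is open. But the diary's stated content is sock wear, reasons for removal and comments, and staff help with the socks only where needed. Unequal reporting is possible but has no demonstrated size.
- **The definitive trial would be mis-sized by a known amount.** Any such figure needs an assumed reporting rate and an assumed incidence. It would treat a rate per tear as a rate per person, and use a yes/no outcome when the proposed primary outcome is skin tear-free days. It would be an error only if the later trial ascertained tears better than the pilot.
- **Timeliness cannot be assessed.** Date and approximate time of injury are recorded, so delay can be described, and timeliness is not a listed pilot outcome. The 24 h figure is an aim and can sit beside a longer limit. The firm contradiction is between Table 1 and the injury procedure.

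**Conclusion.** The point holds in a limited form. The only ascertainment check described measures the completeness of care home records for tears already known. It is silent on tears not telephoned in, does not cover community participants, and is not backed by any stated rule for counting tears that surface at regular contacts. The conclusion about direction follows from the wording and needs no assumed rate; the 80% figures only illustrate it. The document does not allow the number of missed tears, or any bias in incidence, to be estimated.

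The conflict between Table 1 note b and the injury procedure is definite, with upper limits differing by one to four calendar days in the examples shown. Its consequence is modest: compliance cannot be judged against a single standard.

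Neither matter is a safety issue. The first is worth changing because it concerns a named pilot outcome and the remedy is cheap.

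**What to change.** **Ascertainment**

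- At existing care home visits, the nurse reads the accident and wound records of every participant in both arms, covering the period since the last reading, and notes any leg tear not telephoned in. If a week's contact is by telephone, the reading waits for the next visit.
- Community participants in both arms are asked the same fixed question about new leg tears at each regular contact.
- Every tear is logged by how it came to light. This keeps telephoned tears separable from those found by the added checks.
- Report the number and share of known tears that were telephoned in, by arm and by setting, descriptively and with confidence intervals.

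A two-source (Chapman) estimate of the total should not be attempted. The same staff may both write the record and make the call, so the sources are not independent. Events will also be few: at an assumed 20% incidence, 90 × 0.20 = 18 people with a tear, or 18 / 4 = 4.5 per cell if arm and setting are crossed and the cells are equal. The community figure will be the weaker one, since it has no care home record behind it.

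The cost is a little more nurse time per existing visit, more in larger homes, and one log. No extra visits are needed.

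**Windows**

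Reconcile Table 1 note b, the injury procedure and Skin tear assessments into one window with one stated start point. If the 24 h aim is kept, label it as a target within that window. This is a text change only.
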